## Abstract

**Introduction:**

Menstrual distress caused by primary dysmenorrhea is associated with physical and psychological symptoms—before, after, and during menstruation. Leventhal’s self-regulation educational model is based on the cognitive and emotional experiences of threat responses to symptoms and relates to coping responses. This study aims to investigate the effect of the implementation of a psychoeducational intervention, based on the self-regulation model of menstrual distress in adolescents.

**Methods/design:**

In this randomized controlled trial, 120 adolescent girls with moderate to severe menstrual pain (based on visual analog scale (VAS) ≥ 4) from twelve randomly selected high schools in Qazvin City will be enrolled in the study and will be randomly assigned to either a 3-session psychoeducational intervention (*n* = 60) or control (*n* = 60) groups. The sessions will be between 60 and 90 min apiece, and they will run for three consecutive weeks (one session per week). The data collection tools will include questionnaire eliciting menstrual information and demographics, the VAS, the Moos Menstrual Distress Questionnaire, and the illness perception questionnaire. One month prior to the intervention, both groups will participate in an initial assessment to assess the severity of their pain and level of menstrual distress. Finally, all questionnaires will be completed for three consecutive months after the intervention is completed.

**Discussion:**

It is anticipated that findings of this study will provide evidence for the effectiveness of the Leventhal self-regulation model. Implications for improved practice, understanding, and treatment for menstrual distress may also arise.

**Ethical considerations:**

The research protocol will be reviewed by the ethics committee, which is affiliated with the Qazvin University of Medical Sciences (Decree code: IR.QUMS.REC.1398.043).

**Trial registration:**

IRCT20190625044002N1. Registration date: 2019-09-03.

## Background

Dysmenorrhea (i.e., painful menstruation) is one of the most common gynecological problems and is characterized by acute pelvic pain during menstruation [1, 2]. Depending on the pathological and anatomical statuses, dysmenorrhea is divided into two types of primary and secondary dysmenorrhea [3]. Primary dysmenorrhea is the presence of painful menstruation in the absence of pelvic diseases (e.g., endometriosis and pelvic inflammatory disease) or pelvic leiomyoma [4]. The results of a review of 15 primary studies published between 2002 and 2011 showed that the prevalence of primary dysmenorrhea ranged between 16 and 91% in women over the age of 13, and severe dysmenorrhea was reported as being between 2 and 29% [5]. According to a systematic review of Iranian studies (2016), the prevalence of primary dysmenorrhea was 71% [6]. Momenzadeh et al. reported that the prevalence of dysmenorrhea was 52.1% in Iranian girls under 15 [7].

Primary dysmenorrhea is the most common form of chronic pelvic pain that can last for at least 6 months, can be severe enough to disrupt one’s daily life activities, and ultimately lead to medical or surgical treatment. Chronic pelvic pain associated with the patient’s menstrual cycle is referred to as cyclic chronic pelvic pain [3]. Similar to other chronic pains, menstrual pain can act as a stressor and exacerbate psychological distress (e.g., the symptoms of depression and anxiety) [2].

During the management of dysmenorrhea, the relationship between dysmenorrhea and psychological problems are considered by most clinicians [8, 9]. The physical and psychological symptoms of primary dysmenorrhea (i.e., menstrual distress) may occur before, after, and during menstruation [10]. Menstrual distress is one of the most common problems in adolescence, with [11] 75 to 94% of women experiencing the symptoms [12]. Regarding treatment, 58–90% of adult women prefer bed rest as a preventive treatment when they experience menstrual distress [13]. Menstrual distress is generally associated with symptoms such as irritability, tenderness of the breasts, low back pain, skin disorders, fatigue, palpitations, loneliness, nausea, vomiting, abdominal pain, and general weakness [14]. Painful menstruation and menstrual distress are associated with a deterioration of quality of life, as well as negative socioeconomic consequences [7, 15]. About 1% of women over the age of 18 are absent from work 1 to 3 days a month, due to severe dysmenorrhea. About 14% of adolescent girls miss school each month, due to painful menstruation [16, 17]. Given the impact on healthcare, the reduction in school attendance, and potential socioeconomic impacts of menstruation, this is an area that requires more recognition [5].

Despite various treatments for relieving menstrual pain and its associated symptoms, there is a need to find non-pharmacological approaches without causing side effects to adolescents’ general health [4]. Various studies have shown the efficacy of complementary and alternative therapies (e.g., herbal remedies [18–20], exercise [11], heat [21, 22], and hypnosis [23]) at reducing menstrual pain. Cognitive behavioral therapy is one of the non-pharmacological treatments that can effectively relieve dysmenorrhea as psychological factors can exacerbate pain [24].

The Leventhal self-regulation model is used to understand illness perceptions [25] and provides a framework for the organization of individuals’ perceptions about health, illness, and outcomes. This theory describes cognitive processes, emotional responses, and consequences of behaviors associated with health and illness [26]. Illness perceptions include responses to symptoms (e.g., weakness and lethargy) by directing cognitive and emotional experiences to related threats (e.g., dysmenorrhea) and guiding coping responses [27]. The model posits that people’s cognitive perceptions about illness are related to five dimensions, which include beliefs about identity (e.g., related to diagnosis or symptoms of the disorder), causes (e.g., ideas about the origins), consequences (e.g., the impact on different aspects of life), timelines (e.g., thoughts about the duration of the disorder), and treatment or control (e.g., beliefs about the treatment and improvement of the disorder). Emotional perceptions also include negative reactions including fear, anxiety, anger, and discomfort [25].

Illness perceptions can affect health-related behaviors and adaptive behaviors that the patient requires to be able to manage, or cope with, a disease [28]. Research shows that a person’s understanding of a disease is an important determinant of self-care [29]. A lack of awareness about one’s illness can result in a type of vulnerability, which can in turn cause anxiety about the treatment process. In fact, education based on the self-regulation model can raise awareness, which can reduce anxiety and concerns [30].

The chronic nature of primary dysmenorrhea, its prevalence, and symptoms are major factors that disrupt quality of life and social activities for female adolescents. There is also a widely understood gender inequality in medical research resulting in a dearth of research on menstruation problems and women’s health issues more generally [31]. Therefore, this study will aim to investigate the effects of psychoeducational intervention using the Leventhal self-regulation model during menstrual distress in adolescent girls with primary dysmenorrhea.

## Methods

### Study design and participants

The design of this randomized controlled trial is designed based on standards devised by the Consolidated Standards of Reporting Trials (CONSORT) (Fig. 1). Adolescent girls aged 14–19, attending high schools in Qazvin City, and experiencing moderate to severe pain (pain intensity ≥ 4 based on the participant’s VAS score for two consecutive months in a preliminary screening) will be recruited to the study. Inclusion criteria will include having regular menstruation and experiencing menstruation for at least 2 years. Girls will be excluded from the study if they have experienced secondary dysmenorrhea due to endometriosis, adenomyosis, subacute endometritis, pelvic inflammatory disease, intrauterine devices, ovarian cysts; congenital anomalies of the pelvis and stenosis; history of gynecological surgery; or report a history of mental or physical illnesses or substance abuse (based on their self-report and student’s health reports). Participants will also be excluded if they are married or have taken specific medications for premenstrual syndrome (e.g., fluoxetine) in the past 6 months.

**Fig. 1 Fig1:**
[figure not shown]
CONSORT flow diagram

### Sample size estimation

The estimation of the sample size is based on the study of Wong et al. considering the mean menstrual distress score for intervention group 23.96 ± 4.79 and 26.61 ± 5.1 in the control group [32], alpha = 0.05, and *β* = 0.2; the estimated sample size in each group will be 51 individuals in each group. Peng et al. suggested adding a 20% attrition rate for youth, school-based studies [33], so the estimated sample size for the current study will be 60 individuals for each group. As we have two groups, the total sample will be 120 female students.

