### Sampling and randomization

Given the likelihood of information sharing between the students at the same school, the intervention and control groups will be selected from separate schools. A two-stage cluster sampling design will be used to selected study samples. At the first stage, twelve schools will be randomly selected from a list of eligible schools (girls-specific schools and not involved in similar educational intervention) in Qazvin city using a computer-generated random number. The list of schools will be provided by the department for Education in Qazvin. At the second stage, one class will be randomly selected from each school through a simple random method. Ten eligible individuals will be selected using random sampling method. Assigning of schools to the control and intervention groups will be done via random sampling method. Therefore, six schools will be assigned to the intervention, and six schools will be assigned to the control group.

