### Data analysis method

Collected data will be analyzed on an intention-to-treat basis using MLwin 2.27 [41]. ICC will be calculated within groups and a three-level mixed model will be used with adolescents girls nested in schools. The significance level will be *p* < 0.05. Finally, power of study will be calculated too.

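### The sample size is calculated as if girls were individually randomised, although 12 schools are randomised (six per arm), so the stated 80% power is not supported

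*Protocol article*

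**What the plan says.** The section Sample size estimation takes the "mean menstrual distress score for intervention group 23.96 ± 4.79 and 26.61 ± 5.1 in the control group" from an earlier study, sets alpha at 0.05 and beta at 0.2, and states that "the estimated sample size in each group will be 51 individuals in each group". It cites a source that "suggested adding a 20% attrition rate for youth, school-based studies" and concludes that "the estimated sample size for the current study will be 60 individuals for each group", 120 in all. It names no ICC, design effect, cluster size or number of schools.

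The section Sampling and randomization draws twelve schools, one class per school and ten eligible girls per class, and allocates by school: "six schools will be assigned to the intervention, and six schools will be assigned to the control group". It keeps the arms in separate schools because girls at one school are likely to share information.

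The section Data analysis method recognises the clustering: "ICC will be calculated within groups and a three-level mixed model will be used with adolescents girls nested in schools". It ends: "Finally, power of study will be calculated too". The abstract, by contrast, says that the 120 girls "will be randomly assigned to either a 3-session psychoeducational intervention" or to control.

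**The concern.** Clustering is in the allocation and in the analysis but not in the sample size. Girls in the same class of the same school tend to resemble one another, so 60 girls in six schools carry less information on the arm difference than 60 independently randomised girls. With 12 randomised units, the between-school variation is also estimated on only 10 degrees of freedom.

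At stake is a stated design property. A beta of 0.2 tells the reader that a null result on the primary outcome, menstrual distress, counts fairly strongly against the planned effect. If the design does not have that power on the basis given, a null result will be over-read. The abstract adds to this, because it reads as an individually randomised trial.

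**Working it through.** **Inputs from the protocol article.** Means 23.96 and 26.61, SDs 4.79 and 5.1, alpha 0.05, beta 0.2, 51 then 60 per group, 20% attrition (Sample size estimation); six schools per arm, ten girls per school (Sampling and randomization). **Assumed here:** a two-sided test, since sidedness is not stated, and a school ICC of 0.01, 0.05 or 0.10, since none is given. ICC 0 is shown as a reference.

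**Step 1: the plan's own figure.** Difference = 26.61 - 23.96 = 2.65. Pooled SD = sqrt((4.79² + 5.1²)/2) = 4.947. Standardised effect d = 2.65/4.947 = 0.536. For individual randomisation, n per arm = 2(1.960 + 0.842)²/d² = 54.7, that is 55 (56 with the t distribution). The stated 51 is not reproduced. One-sided 80% power gives 44, two-sided 90% gives 74, and an SD of 4.79 in both arms gives 52. On the two-sided reading, 51 is below the unclustered requirement, so it holds no allowance for clustering. On the one-sided reading it would exceed 44, but the section shows no inflation step that would explain the gap.

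**Step 2: attrition.** 51/(1 - 0.2) = 63.75, so 64; 51 × 1.2 = 61.2, so 62. Sixty is short of both. A 20% loss from 60 leaves 48 per arm, or 8 per school.

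**Step 3: power with six schools per arm.** Design effect DE = 1 + (m - 1) × ICC, effective n per arm = 6m/DE, noncentrality = d × sqrt(effective n/2). Power is taken from the noncentral t on 12 - 2 = 10 degrees of freedom and, for comparison, from the normal distribution. This is one unadjusted post-intervention comparison, the basis that the sample size section uses.

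| Girls per school (m) | ICC | DE | Effective n per arm | Noncentrality | Power, t(10) | Power, normal |
|---|---|---|---|---|---|---|
| 10 | 0 | 1.00 | 60.0 | 2.93 | 75% | 83% |
| 10 | 0.01 | 1.09 | 55.0 | 2.81 | 72% | 80% |
| 10 | 0.05 | 1.45 | 41.4 | 2.44 | 59% | 68% |
| 10 | 0.10 | 1.90 | 31.6 | 2.13 | 49% | 57% |
| 8 | 0 | 1.00 | 48.0 | 2.62 | 66% | 75% |
| 8 | 0.01 | 1.07 | 44.9 | 2.54 | 63% | 72% |
| 8 | 0.05 | 1.35 | 35.6 | 2.26 | 53% | 62% |
| 8 | 0.10 | 1.70 | 28.2 | 2.01 | 44% | 52% |

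**Step 4: where 80% is reached.** With the normal reference and no loss, the break-even ICC is (60/54.7 - 1)/9 = 0.011. With the planned loss, or with 10 degrees of freedom, 80% is not reached even at ICC 0.

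**Step 5: detectable effect.** At ICC 0.05 on t(10), the effect detectable with 80% power is 0.68 SD with ten girls per school and 0.74 SD with eight, against the planned 0.536 SD.

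**The case against.** The strongest reply is that the table does not model the planned analysis. The protocol collects pre-intervention distress and three consecutive months of follow-up, and it plans a three-level mixed model, whose natural third level is the repeated measurement. Suppose a within-girl correlation of 0.6, with all the gain at the within-school level. Averaging three follow-ups multiplies the within-school variance by (1 + 2 × 0.6)/3 = 0.733, and baseline adjustment lowers this to 0.733 - 0.36 = 0.373. With these factors f, the variance of a school mean is ICC + (1 - ICC) × f/m in SD² units. At ICC 0.05 and ten girls per school, power on t(10) is then 68% with averaging (76% normal) and 82% with both (89% normal); with eight girls and both it is 78% (86% normal). At ICC 0.10 with ten girls and both it is 63% (72% normal). This stands as a possibility. It does not support the stated figure, because the protocol fixes neither the correlation nor baseline adjustment, and its calculation claims credit for neither.

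Four stronger readings are tempting, and the documents do not support them.

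- A reader might infer that the trial has roughly even odds of detecting the planned effect. That rests on the upper part of an assumed ICC range and on one unadjusted measurement.
- A reader might turn 0.68-0.74 SD into 3.4-3.7 questionnaire points. The questionnaire is described as 47 items scored 1 to 4, so its lowest total is 47, and the planning means of 23.96 and 26.61 cannot be totals on that form. A short form of 16 to 19 items is also mentioned. The points cannot be tied to the trial's outcome.
- A reader might dismiss the closing power calculation as a restatement of the p-value. That is so if it uses the observed effect, but it may instead mean the planned effect with the observed ICC. On either reading it comes too late to justify the size.
- A reader might infer that the analysis ignores clustering. It does not; the mixed model addresses the type I error but does not restore the power.

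It is also fair to say that the abstract's wording is minor, since it names the twelve schools and the methods section is explicit.

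**Conclusion.** The point holds as a mismatch between the sample size calculation and the design. The protocol states its method, inputs, error rate and result, and the method is that of an individually randomised trial. This is therefore not a detail left out of a condensed article, and a later analysis plan could not change the basis on which 120 was chosen.

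On the protocol's own single-comparison basis, 80% power is met only if no girl is lost, the ICC is at most about 0.011 and a normal reference is used. Otherwise it is 49-72% on t(10) (57-80% normal) with full retention and 44-63% (52-72% normal) after 20% loss, for ICC 0.01-0.10. These ranges rest on an assumed ICC, a two-sided test and one unadjusted measurement. They show that the stated beta is unsupported. They do not give the power of the planned repeated-measures model, which cannot be computed from what the protocol states.

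**What to change.** Keep 12 schools and 120 girls, and change the text as follows.

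- **Sample size estimation:** rewrite it as a cluster-randomised calculation with six schools per arm, 8-10 girls analysed per school, an assumed ICC with a range and its basis, design effect 1 + (m - 1) × ICC, and 10 between-school degrees of freedom. State the sidedness, and correct the 51 and the attrition step at the same time. Either restate the power as a range labelled with these assumptions, or recompute it for the planned mixed model with a stated within-girl correlation and a statement on baseline adjustment. Give any detectable difference in SD units.
- **Abstract:** say that schools are randomly assigned.
- **Data analysis method:** replace the closing power calculation with the arm difference and its 95% CI, and the ICC with its CI.

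The cost is wording and a less favourable stated power; no further girls are needed. The change corrects the claim and does not raise the power. If the sponsor wants 80% on the single-comparison basis, with ten girls analysed per school and the t correction, it would take 8, 10 or 12 schools per arm at ICC 0.01, 0.05 or 0.10.

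### The 51 per group does not follow from the stated means, SDs, alpha and beta (55 does), and 60 per group leaves only 48 after the stated 20% attrition.

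*Protocol article*

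**What the plan says.** The Sample size estimation section of the protocol article prints every input. Using figures from an earlier study, it takes the "mean menstrual distress score for intervention group 23.96 ± 4.79" and "26.61 ± 5.1 in the control group", with alpha 0.05 and beta 0.2. From these it states that "the estimated sample size in each group will be 51 individuals in each group". It then cites a source that "suggested adding a 20% attrition rate for youth, school-based studies", and ends: "so the estimated sample size for the current study will be 60 individuals for each group", for 120 girls in total.

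The Sampling and randomization section reaches the same total another way: ten girls from each of twelve schools, where "six schools will be assigned to the intervention, and six schools will be assigned to the control group". The sample size section mentions no unequal allocation, baseline adjustment, repeated-measures gain or design effect.

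**The concern.** The section gives inputs, an intermediate result and a final result, so each step can be checked directly. Two things look wrong. The 51 is too small for the difference and SDs quoted. The 60 is too small to leave 51 after one girl in five is lost.

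Both slips make the trial smaller than its own assumptions require, so they add up. This is the only sample-size justification given, and it concerns menstrual distress, the primary outcome. If it is wrong, readers are told that the trial has 80% power when, on its own assumptions, it has less.

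**Working it through.** **Inputs (all from Sample size estimation)**
- Difference in means: 26.61 − 23.96 = 2.65
- SDs: 4.79 (intervention) and 5.1 (control). Root-mean-square SD = √((4.79² + 5.1²)/2) = 4.947, so the standardised difference is 2.65/4.947 = 0.536
- Alpha 0.05, with sidedness not stated. Two-sided is assumed and one-sided is also tried
- Beta 0.2, so power 80%
- Equal arms, consistent with six schools per arm
- Attrition 20%

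**Step 1: trying to reproduce 51**

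n per group = (z_α + z_β)² × (SD₁² + SD₂²) / difference²

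Two-sided, both stated SDs: (1.960 + 0.842)² × (4.79² + 5.10²) / 2.65² = 54.7, so **55**. An exact t-test calculation gives 56.

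| Variant | n before rounding | Rounded up |
|---|---|---|
| Both SDs, two-sided | 54.7 | 55 |
| Arithmetic mean of the SDs, two-sided | 54.7 | 55 |
| 5.1 in both arms, two-sided | 58.1 | 59 |
| 4.79 in both arms, two-sided | 51.3 | 52 |
| Both SDs, one-sided | 43.1 | 44 |

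Only 4.79 in both arms comes near 51. It ignores the control SD that the section itself quotes, and it must then be rounded down.

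**Step 2: attrition**
- Enrolled 60, loss 20%: 60 × 0.8 = **48** remain, fewer than 51
- Correct inflation of 51: 51/0.8 = 63.75, so 64 per group
- The shortcut of adding a fifth: 51 × 1.2 = 61.2, still above 60
- Correct inflation of 55: 55/0.8 = 68.75, so **69** per group, 138 in total
- Loss at which 60 still leaves 51: 1 − 51/60 = 15%
- Loss at which 60 still leaves 55: 1 − 55/60 = 8.3%

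**Step 3: power with both stated SDs (two-sided 0.05, individual randomisation)**

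| Evaluable per group | Normal approximation | t test |
|---|---|---|
| 48 (60 with 20% loss) | 74.7% | 73.8% |
| 51 | 77.2% | 76.4% |
| 55 | 80.2% | 79.5% |
| 56 | 80.9% | 80.2% |
| 60 (no loss) | 83.5% | 82.9% |

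**Step 4: direction of the clustering effect (illustration only)**

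The documents give no intraclass correlation, so 0.02 and 0.05 are assumed. With eight evaluable girls per school (48/6), the design effect is 1 + 7 × ICC.
- ICC 0.02: 48/1.14 = 42.1 effective per arm, power about 69%
- ICC 0.05: 48/1.35 = 35.6 effective per arm, power about 62%

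Both use the normal approximation, with no correction for the small number of schools.

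**The case against.** The best defence is that the errors are small and the planned analysis is not the one in the formula.

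- **Size.** Step 1 is out by four girls per arm, and the effect size comes from a single earlier study whose uncertainty probably matters more. That is fair as to scale, but uncertain inputs do not excuse an output that does not follow from them. After attrition the gap grows to nine per arm.
- **Attrition wording.** The section speaks of "adding a 20% attrition rate for youth, school-based studies", which can be read as 51 × 1.2 = 61.2. Sixty is then a near miss, perhaps rounded to six schools of ten. This is a plausible explanation of how 60 arose, though the text does not say so. The number still leaves 48 after the loss the section itself assumes.
- **Power might be adequate anyway.** With no loss, 60 per group gives about 83%. Questionnaires are repeated over three months, and a mixed model can use partial follow-up. If the effect were the three-month average, with an assumed within-girl correlation of 0.3 to 0.7, the variance would shrink by a factor of (1 + 2ρ)/3, that is 0.53 to 0.80. Forty-eight per group would then have about 84% to 95% power, ignoring clustering. This point stands to the extent that the true power of the final analysis is unknown. But the section claims no such gain, the documents give no correlation, and clustering pulls the other way.
- **55 is not the right size for this design either.** This also stands. Fifty-five answers the individually randomised question that the section poses. It corrects the arithmetic and does not by itself make the calculation fit a trial that allocates schools.

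**Conclusion.** Both steps are wrong as written, and both err towards too few girls. The stated inputs give 55 per group (56 by t test), not 51. Sixty per group leaves 48 at the stated attrition, not 51 or 55. The shortfall is 69 − 60 = 9 enrolled per group, 18 in total. At 20% loss, power is about 74–75% against the stated 80%, so the type II error is about 25–26% rather than 20%.

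These figures rest on a two-sided test, a single comparison of means, both quoted SDs and no clustering. The choice of sidedness does not rescue 51, since one-sided gives 44 with both SDs. The second error does not depend on the formula at all: 60 × 0.8 is below 51 even if 51 is accepted.

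**What to change.** Correct the Sample size estimation section to 55 evaluable per group, state that the test is two-sided, and inflate for attrition by n/(1 − 0.20), which gives 69 per group and 138 in total before clustering.

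If 120 girls is fixed by the plan of twelve schools with ten girls each, keep it and say so. State that 60 enrolled per group with 20% loss leaves 48, and that this gives about 74% power for the assumed difference before the design effect. Add that the 80% target is kept on these inputs only if loss is 8% or less, again before the design effect.

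Make this correction together with the allowance for allocation by school, so that a revised figure of 55 or 69 is not read as sufficient for the cluster design.

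Keeping 120 costs wording only and changes no allocation, outcome or analysis. Enrolling 138 is not a cheap change: 69 across six schools is 11.5 girls per school, so the ten-per-school plan would have to change.
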